## 16.2 Concealment mechanism

The random allocation sequence will be generated using the *ralloc* function in STATA 17/MP for Mac. This allocation sequence will be uploaded into the Royal Victoria Regional Health Centre Research Electronic Database Capture (REDCap®) system (25,26), which is an online, password-protected, web-based research electronic database system stored on the Personal Health Information Protection Act (PHIPA) (27)-protected servers at the Royal Victoria Regional Health Centre. An independent study coordinator not associated with the TDTP will be responsible for accessing the password-protected allocation sequence from REDCap®. Only the study coordinator will have access to the allocation sequence to avoid any influence from the study investigators, TDTP Training Program Coordinator, or other personnel. Allocation concealment will be ensured as the study coordinator will not release the randomisation code until each cohort has completed registration of all of its TDTP students.

## 16.3 Implementation

Cohort randomization will be requested by the TDTP Training Program Coordinator from the independent study coordinator (Section 16.2) 1 week prior to that cohort’s TDTP start date by calling a centralized study telephone number. The study coordinator will access the random allocation sequence through REDCap®, and then inform the Training Program Coordinator of the allocation for the cohort. The Training Program Coordinator will provide this allocation information to the TDTP students. Informed consent from each interested TDTP student in the randomized cohorts ICM^1x^ will then be obtained by *TeachMeToBuild* study personnel (Section 15).

# 17 Masking

This is an open-label, pragmatic study so neither study participants nor Community Builders® nor study personnel, including data analysts, will be masked to the allocation.

# 18 Data Collection

## 18.1 Methods

All demographic and study-related data inputted into the web-based Distress Thermometer screening tool by TDTP students and personnel will be encrypted for transfer and storage in a Microsoft Azure SQL Database. None of the data related to the Distress Thermometer screening tool will be stored locally on the tablet computer. All routinely collected data during clinical encounters will be collected by the MH&A healthcare providers and stored in MEDITECH Expanse, the electronic health record system used at the Royal Victoria Regional Health Centre. Any other study-specific data will be collected by study personnel and stored in electronic case report forms created in REDCap®.

### 18.11 Distress Thermometer data

**All** data variables will contain an option in the drop-down list that states “Rather not say”

| Data | Description | Data type |
| --- | --- | --- |
| **Demographics** | | |
| Age | Years | Integer |
| Date of birth | mmddyy | Continuous |
| Gender identification | Man (cis & transgender) | Categorical |
|  | Woman (cis and transgender) |  |
|  | Non-binary (neither solely man nor woman) |  |
| Country of birth | Canadian-born | Categorical |
|  | Foreign-born |  |
| Education | Below high school graduation | Categorical |
|  | High school diploma |  |
|  | Trades (includes certification or diploma from vocational school or apprenticeship training) |  |
|  | College (includes non-university certificate or diploma from community college, CEGEP, school of nursing and similar programs, university certificate below bachelor’s level) |  |
|  | University (includes bachelor’s degree and university degree or certificate above bachelor’s degree) |  |
| Ethnic/Cultural origin | North American Indigenous | Categorical |
|  | Other North American |  |
|  | European |  |
|  | Caribbean |  |
|  | Latin, Central, South America |  |
|  | African |  |
|  | Asian |  |
|  | Oceania |  |
| Visible minority | Visible minority (persons, other than Indigenous peoples, who are non-Caucasian in race or non-white in colour) | Categorical |
|  | Not a visible minority |  |
| Indigenous group | First Nations | Categorical |
|  | Status |  |
|  | Non-status |  |
|  | Métis |  |
|  | Inuk/Inuit |  |
| Children | None | Categorical |
|  | 1 |  |
|  | 2 |  |
|  | >2 |  |
| In the last **10 years**, have you had: | | |
| Criminal offence | Yes | Categorical |
|  | No |  |
| Mental health disorder | Yes | Categorical |
|  | No |  |
| Substance use disorder | Yes | Categorical |
|  | No |  |
| **Distress Thermometer** | | |
| Visual analog scale | 0-10 | Integer |
| Distress sources | Mental health | Categorical |
|  | Substance use/cravings |  |
|  | Family/Relationships |  |
|  | Financial |  |
|  | Physical health |  |
|  | Work program |  |
|  | Housing |  |
|  | Change in medication |  |
|  | Legal Issues |  |
| Distress question | Yes | Categorical |
|  | No |  |
| **Case Manager** | | |
| Action | Case Manager counselling/support | Categorical |
|  | External service consult (not related to MH&A) |  |
|  | External service consult (Mental health) |  |
|  | External service consult (Addictions) |  |
| Date/Time (Action) | ddmmyy:hh | Continuous |
| Case management time | 0.15 hr units | Continuous |
| Apprentice attendance (Daily (M-F) for 12-week TDTP) | Yes | Categorical |
|  | No |  |
|  |  |  |

### 18.12 Routinely collected data

Any clinical encounters with a healthcare provider for any reason may require the collection of personal health information, such as Ontario Health Insurance Plan number, along with other information as dictated by the healthcare provider, healthcare facility, and diagnostic and therapeutic care plan. The PHIPA-compliant storage and transmission of this routinely collected clinical data will be the responsibility of the health information custodian. This study has no requirements for the *a priori* collection of any routinely collected clinical data.

Other routinely collected data specific to the TDTP includes daily attendance and program completion. The Training Program Coordinator is responsible for this data collection. The daily attendance data will be collected using the Distress Thermometer screening tool. Program completion data will be collected at the end of the 12-week TDTP and entered into the electronic case report form in REDCap by study personnel.

### 18.13 Study-specific data

| Data | Description | Data type |
| --- | --- | --- |
| **Cluster criteria** |  |  |
| City | Barrie vs Sudbury | Categorical |
| Enrollment | Quarter-year  Quarter (Q):  Q1=January 1 – March 31  Q2=April 1 – June 30  Q3=July 1 – September 30  Q4=October 1 – December 31 | Categorical |
| **Primary Outcomes** |  |  |
| Program completion | Yes | Categorical |
|  | No |  |
| Employment (full-time at 24 months) |  | Categorical |
| Self-report | Yes | Categorical |
|  | Employer verified |  |
|  | Employer not verified |  |
|  | No |  |
| **Secondary Outcomes** |  |  |
| Date/Time |  | Continuous |
| Mental health consult | ddmmyy:hh |  |
| Addictions consult |  |  |
| TDTP Satisfaction Survey | National Centre for Vocational Education Research Student Outcomes Survey (21) | Categorical |
| Distress Thermometer |  |  |
| Acceptability survey | Section 12.25 | Categorical |
| Feasibility survey | Section 12.26 | Categorical |

#### 18.13a Foundational skills

Complete essential skills self-assessment for the trades questionnaire (28). There are 9 foundational skills identified in the questionnaire, each containing statements that require the apprentice to answer *yes, somewhat or no.*  For any skills sub-domain in which the apprentice answers *somewhat* and/or *no* in less than 5 statements, the apprentice is considered to possess a *strength* in that foundational skill. A cumulative score of the number of foundational skills that each apprentice possesses (out of 9) will be calculated and used as a baseline variable. Each apprentice will be asked to complete this survey as part of the routine orientation process. The survey link will be provided to each apprentice and all results will be stored in REDCap using a unique identifier number.

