# 13 Participant timeline

| Activity | Study Period (Days) | | | | |
| --- | --- | --- | --- | --- | --- |
|  | T-1 | T0 | T1 | T2 | T3 |
|  | -7 | 0 | 1-60 (M-F) | 61-70 | 800 |
| **Enrollment** | | | | | |
| Cohort Randomization | x |  |  |  |  |
| Informed Consent |  | x |  |  |  |
| Demographics |  | x |  |  |  |
| Foundational skills survey |  | x |  |  |  |
| **Interventions** | | | | | |
| Distress Thermometer screening |  |  | x |  |  |
| MH&A program |  |  | x |  |  |
| **Assessments** | | | | | |
| TDTP Attendance |  |  | x |  |  |
| TTDP Completion |  |  |  | x |  |
| Employment |  |  |  |  | x |
| Time to Access MH&A |  |  |  | x |  |
| Healthcare utilization |  |  |  | x |  |
| TDTP Satisfaction survey |  |  |  | x |  |
| Case management utilization |  |  |  | x |  |
| Distress Thermometer tool |  |  |  |  |  |
| Acceptability |  |  |  | x |  |
| Feasibility |  |  |  | x |  |
| Compliance |  |  |  | x |  |

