## 14.1 Difference in proportion of AFDs

The sample size is fixed at approximately 448 individuals. We anticipate that the first few cohorts will be asked to pilot the screening tool, potentially removing up to 50 apprentices from the final sample size. We will use a fixed sample size of 400 apprentices, divided equally between Sudbury and Barrie sites. The expected cohort sizes will range from 6 to 10 apprentices, resulting in 20 to 34 cohorts per site. We will use a 3-level hierarchical design to model differences in proportion of AFDs where the daily attendance (Level 1) will be coded as binary; 0 for absence and 1 for attendance. Level 1 observations are clustered within individual apprentices (Level 2), which are nested within individual cohorts (Level 3). The sites (Sudbury and Barrie) and start date of cohort enrollment (q1 (January-March); q2 (April-June); q3 (July-Sept); q4 (Oct-Dec) and year) will be included as confounding variables in Level 1 and will not enter into the power calculations. Using this design, we performed a sensitivity analysis to determine the power to observe different primary outcome effect sizes with an $\alpha$-level 0.05**.**  As can be seen in the following table, even small differences in attendance (5% difference in proportions of AFDs) would still be detected with power ≥ 80% as long as the Level 2 inter-cluster correlation ≤ 0.125, a very reasonable assumption as there is no reason to believe that these apprentices’ attendance behaviours will be highly correlated with each other (23).

|  | **Scenarios**^1^ | | | | | | | |
| --- | --- | --- | --- | --- | --- | --- | --- | --- |
| **Variables** | 1 | 2 | 3 | 4 | 5 | 6 | 7 | 8 |
| Test Significance Level, α​ | 0.05 | 0.05 | 0.05 | 0.05 | 0.05 | 0.05 | 0.05 | 0.05 |
| Mean Difference, δ = µ₁ - µ₂​ | 0.1 | 0.15 | 0.05 | 0.05 | 0.05 | 0.05 | 0.05 | 0.1 |
| Standard Deviation, σ​ | 0.1 | 0.1 | 0.1 | 0.1 | 0.1 | 0.1 | 0.15 | 0.15 |
| Level 1 Unit Correlation, ρ₁​ | 0.75 | 0.75 | 0.75 | 0.75 | 0.75 | 0.75 | 0.75 | 0.75 |
| Level 2 Unit Correlation, ρ₂​ | 0.5 | 0.5 | 0.5 | 0.25 | 0.125 | 0.05 | 0.05 | 0.05 |
| Number of Level 3 Units in Group 1, C₁​ | 15 | 15 | 15 | 15 | 15 | 15 | 15 | 15 |
| Number of Level 3 Units in Group 2, C₂​ | 15 | 15 | 15 | 15 | 15 | 15 | 15 | 15 |
| Level 3 Units per Group Ratio, C₂/C₁​ | 1 | 1 | 1 | 1 | 1 | 1 | 1 | 1 |
| Number of Level 2 Units per Level 3 Unit, K​ | 6 | 6 | 6 | 6 | 6 | 6 | 6 | 6 |

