### 20.11 Primary

#### 20.11a Program attendance

We will use a 3-level hierarchical design to model the program attendance data where the observation for each day (Level 1) will be coded as binary; attendance (=1) versus absence (=0). Level 1 observations are clustered within individual apprentices (Level 2) , which are nested within cohorts (Level 3). We will analyse the outcome data using multi-level, mixed-effects logistic regression analysis with fixed effects estimated for the variance in the intercepts of both apprentice and cohort levels. The interventions (Distress thermometer and MH&A) will be included as well as a variable for their interaction effect. We will also include time period (year-quarter) and an interaction term between the time period and each intervention (Distress thermometer and MH&A). A sensitivity analysis will be conducted to compare this baseline model with an extended model that includes any baseline demographic or clinical variables that appear to be unbalanced at Level 1. The models will be compared using the likelihood-ratio comparison test for superiority. Post-regression analyses using *margins* command will be used to estimate difference in program attendance between treatment groups.

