#### 20.11b Program completion

We will use a logistic multivariate regression analysis to model program completion where the observation for program completion will be coded as binary: completion (=1) and drop-out (=0). The interventions (Distress thermometer and MH&A) will be included as well as a variable for their interaction effect. We will also include time period (year-quarter) and an interaction term between the time period and each intervention (Distress thermometer and MH&A). Clustered robust standard errors will be used to account for cohort intra-cluster correlation. Post-regression analyses using *margins* command will be used to estimate difference in program completion between treatment groups.

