#### 20.11c Post-program employment

We will use a logistic multivariate regression analysis to model post-program employment where the observation for post-program employment will be coded as binary: full-time (=1) and not full-time (=0). The interventions (Distress thermometer and MH&A) will be included as well as a variable for their interaction effect. We will also include time period (year-quarter) and an interaction term between the time period and each intervention (Distress thermometer and MH&A). Clustered robust standard errors will be used to account for cohort intra-cluster correlation. Post-regression analyses using *margins* command will be used to estimate difference in post-program employment between treatment groups.

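### The foundational skills score is declared a baseline variable, but none of the three primary main models uses it; pre-specifying it as a covariate is a cheap improvement with a nil to modest gain

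*Protocol*

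**What the plan says.** - **Collection.** Section 18.13a defines a count, out of 9, of the foundational skills in which an apprentice has a strength, taken from a self-assessment questionnaire. "Each apprentice will be asked to complete this survey as part of the routine orientation process". The score "will be calculated and used as a baseline variable".
- **Completion.** Section 20.11b: "We will use a logistic multivariate regression analysis to model program completion". The listed terms are the two interventions, their interaction, year-quarter and year-quarter by intervention. Standard errors are clustered on cohort, and margins give the difference in proportions.
- **Employment.** Section 20.11c: "We will use a logistic multivariate regression analysis to model post-program employment", with the same terms.
- **Attendance.** Section 20.11a has the same fixed terms in its main model. A sensitivity analysis compares it with an "extended model that includes any baseline demographic or clinical variables that appear to be unbalanced at Level 1".
- **Timing.** Section 13 puts cohort randomisation at day -7 and the skills survey at day 0. Section 16.3: "The Training Program Coordinator will provide this allocation information to the TDTP students". Section 17 makes the trial open-label.
- **Size.** Section 14.1: "We will use a fixed sample size of 400 apprentices, divided equally between Sudbury and Barrie sites".

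**The concern.** The protocol collects a plausible prognostic variable and names it a baseline variable, then writes out its primary models without it. Section 5.13 describes people with low education or low life and literacy skills as the usual targets of such programs, before listing additional barriers to completion and employment. A skills score is therefore a natural candidate covariate.

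The sample size is fixed, so covariate adjustment is one of the few remaining ways to gain precision. By the protocol's own table in Section 14.2, completion power is about 70% at a control proportion of 0.75 and reaches about 80% only at 0.80 with no intracluster correlation. Employment has no calculation of its own (Section 14.3). With a limited number of cohorts, the randomised tool arms can also differ by chance in apprentice skills, and the listed models leave any such difference in the estimate.

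The outcomes are also handled unevenly. Attendance has a covariate-extended sensitivity model, while completion and employment have none, and no reason is given.

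**Working it through.** **1. Where the score could enter**

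| Outcome | Score in main model | Covariate-extended model |
|---|---|---|
| Attendance (20.11a) | no | yes, for demographic or clinical variables that look unbalanced |
| Completion (20.11b) | no | none |
| Employment (20.11c) | no | none |

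The gap in the main models covers all three outcomes. Whether a skills score counts as demographic or clinical in 20.11a is not stated.

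**2. The protocol's own power figures (Section 14.2)**

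Inputs: two-sided alpha 0.05, difference 0.10, control 0.75 or 0.80, 20 x 10, 33 x 6 or 25 x 8 per group, ICC 0 (0.05 in scenario 2). Effective n per group = K x m / [1 + (m - 1) x ICC]. Power = Phi[(0.10 - 1.96 x SE0) / SE1], with SE0 from the pooled proportion and SE1 from the two separate proportions.

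Scenario 1: n = 200, SE0 = sqrt(2 x 0.8 x 0.2 / 200) = 0.0400, SE1 = sqrt((0.1875 + 0.1275) / 200) = 0.0397. Power = Phi[(0.10 - 0.0784) / 0.0397] = 70.7%; the protocol states 70.6%.

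All seven scenarios give 70.7, 54.7, 70.2, 70.7, 80.2, 79.8 and 80.2%, against the stated 70.6, 54.6, 70.2, 70.6, 80.2, 79.8 and 80.2%. They reproduce.

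**3. Power with the score added**

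The protocol gives no association between score and outcome, so R2 (the share of outcome variance that the score explains) is an assumption. Multiplying the variance of the risk difference by (1 - R2), with 200 per group and cohorts of 10:

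| Control, ICC | R2 = 0 | 0.02 | 0.05 | 0.10 | 0.15 |
|---|---|---|---|---|---|
| 0.75, 0 | 70.7 | 71.6 | 72.9 | 75.2 | 77.6 |
| 0.75, 0.05 | 54.7 | 55.5 | 56.8 | 59.1 | 61.6 |
| 0.80, 0 | 80.2 | 81.0 | 82.2 | 84.2 | 86.2 |

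A simulation of the margins-type risk difference (unclustered, control 0.75) supports the factor. At log-odds slopes of 0, 0.2, 0.4, 0.6 and 0.8 per SD, the adjusted-to-unadjusted variance ratio was 1.00, 0.99, 0.98, 0.94 and 0.90. R2 for the four nonzero slopes was 0.008, 0.029, 0.062 and 0.101.

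**4. Direct simulation of power**

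200 per group, ICC 0, normal covariate, Wald test of the treatment term, without and then with the score; 3,000 trials per setting (6,000 for slopes 0.3 and 0.5):

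| Log-odds slope per SD | Control 0.75 | Control 0.80 |
|---|---|---|
| 0 | 69.9, 69.7 | 80.6, 80.6 |
| 0.3 | 71.5, 72.1 | 80.9, 81.3 |
| 0.5 | 70.2, 71.7 | 80.9, 81.9 |
| 0.7 | 70.9, 74.1 | 79.7, 81.7 |
| 1.0 | 71.7, 77.3 | 80.5, 85.3 |

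The simulation error of a single power near 70% is sqrt(0.7 x 0.3 / 3,000) = 0.8 points, which is why the unadjusted figures vary between rows. A run with a 0-9 score in place of the normal covariate gave about 0 to 2 points at slopes of 0.3 to 0.7 and about 5 to 6 points at 1.0.

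**5. Chance imbalance in the score, randomised tool comparison**

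95% half-width in SD units = 1.96 x sqrt(2 x [1 + (m - 1) x ICC] / n).

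- 200 per group, cohorts of 10: 0.20 at a score ICC of 0; 0.27 at an assumed 0.10.
- About 100 per cell (ICM^10^ against BCM within Sudbury): 1.96 x sqrt(2/100) = 0.28; at an assumed ICC of 0.10, 1.96 x sqrt(2 x 1.9/100) = 0.38.

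**6. Order of events**

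Randomisation (day -7), disclosure to students, then a self-rated survey (day 0). The score is therefore not protected from knowledge of allocation.

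**The case against.** The strongest reply is that nothing here is an error. Calling a variable baseline is satisfied by describing the cohorts or checking balance, an unadjusted logistic model is valid for the randomised tool comparison, and choice of covariates is commonly left to an analysis plan, which is not at hand. This stands against any claim of contradiction. It does not remove the point, because the protocol itself lists the model terms and gives the score no role among them.

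Four stronger readings are tempting, and the protocol does not support them:

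- **That only completion and employment are affected.** The attendance main model omits the score too.
- **That the precision is free.** Apprentices are only asked to complete the survey, no association with outcome is documented, and Section 15 already screens entrants for basic speaking and writing skills, which may narrow the range. At slopes of 0.3 to 0.5 the simulated gain is only 0.4 to 1.5 points.
- **That adjustment cannot bias the comparison.** This holds for covariates fixed before allocation is known. Here the self-rating follows disclosure. MH&A is tied to site (Sections 5.3 and 8), and employment is measured among graduates (Section 12.13), a group formed after randomisation. Adjustment makes neither a clean randomised comparison.
- **That the scoring rule credits a skipped domain as a strength.** This presumes that domains can be left blank. The survey is stored in REDCap, where Section 19 describes rules to limit missing required fields.

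The simulations also simplify. They have no clustering and no quarter or interaction terms, they use 200 per group although the primary objectives compare single cells, and employment was not simulated. The figures therefore indicate the size of the gain and do not predict it.

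**Conclusion.** The point holds as a cheap improvement. A score sought from each apprentice and labelled a baseline variable appears in none of the three primary main models, and completion and employment lack even the extended model given for attendance. On completion power, the expected gain is about 0 to 3 points for log-odds slopes of 0 to 0.7 per SD and about 5 to 6 points at 1.0, with essentially no loss if the score is uninformative. These figures assume 200 per group, no clustering and a prognostic strength that the protocol does not supply. Protection against chance imbalance extends only to the randomised self-report tool. None of this makes a stated figure or the unadjusted tool analysis wrong.

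**What to change.** - Add the score (0-9, linear) as a pre-specified fixed covariate in Sections 20.11b and 20.11c. Do the same in 20.11a, in place of selecting covariates because they look unbalanced.
- Keep margins to report the difference in proportions.
- State a simple imputation for missing scores so that no apprentice is dropped.
- Have the survey completed before the cohort's allocation is told to students. Section 16.2 already holds back the randomisation code until a cohort's registration is complete, so the survey could be attached to registration.
- Say in the text that adjustment does not remove the confounding of MH&A with site or the selection of graduates in the employment analysis.

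The cost is one degree of freedom per model, a missing-data rule and a change in survey timing. If the survey stays after disclosure, a small risk of bias from an allocation-influenced self-rating remains and should be acknowledged.

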### 18.14 Healthcare utilization

This data (see Section 12.22) is available from the Registered Persons Database, Ontario Mental Health Reporting System, Discharge Abstract Database, and National Ambulatory Care Reporting System through the Institute for Clinical Evaluative Sciences using a data linkage with each patient’s unique Ontario Health Insurance Plan number.

As a prescribed entity under the Personal Health Information Protection Act (27), the Institute for Clinical Evaluative Sciences is authorized to collect personal health information from health organizations without consent for the purposes of evaluation and monitoring of Ontario’s health system. The Institute for Clinical Evaluative Sciences is prohibited, under its agreements

with data providers, from contacting individuals whose information has been

entrusted to the Institute for Clinical Evaluative Sciences. This contractual obligation restricts any opportunity to seek individuals’ consent for use of their information for research.

The Institute for Clinical Evaluative Sciences will make available a research-ready, linked and risk-reduced coded dataset to the study investigators. Although highly de-sensitized, the research data is presented at an individual level. Study investigators will access the Research Data remotely on a secure, encrypted VMware virtual desktop called the Institute for Clinical Evaluative Sciences Data & Analytic Virtual Environment (IDAVE). Study investigators will perform analyses on IDAVE using statistical software. Research Data may not be copied or transferred from IDAVE. Only results derived from the Research Data that have been vetted for

re-identification risk and approved by Institute for Clinical Evaluative Sciences may be released from IDAVE.

